### Methods in analysis to handle protocol non-adherence and any statistical methods to handle missing data {20c}

The membership of each analysis set will be determined and documented, and the reasons for exclusion will be given prior to database lock. A summary table will list the individual participants sorted by treatment group and describe their protocol deviation/violation. Three study populations will be considered in the analysis: two to determine efficacy and one for safety.

Intention-to-treat (ITT) population: All participants with valid informed consent will be included according to the treatment to which they are randomised, regardless of whether they prematurely discontinue treatment or are otherwise protocol violators/deviators. Participants that meet late exclusion criteria will not be included in the intention-to-treat population.

Per-protocol (PP) population: a sub-population of the ITT population where participants will be excluded if they were administered incorrect treatment by the study team (i.e. not given the randomised treatment due to study team error), as well as participants who were not adherent to the randomised study regimen, defined as follows: having missed >2 days of either study drug in the first 2 weeks of induction treatment, i.e. >2 doses of fluconazole or >8 doses of flucytosine.

Safety population: This will be defined as all study participants included in the ITT analysis who received at least one day of any of the study interventions.

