#### Late exclusion criteria

Division of AIDS (DAIDS) grade 4 abnormalities of platelets, neutrophil count, or creatinine level on baseline bloods:Platelets < 25,000 × 10^6^/LNeutrophils < 0.400 × 10^9^/LCreatinine > 3.5 × upper limit of normal (with standardised upper limit of normal [ULN] of 114 µmol/L, this includes any creatinine level ≥ 400 µmol/L)Microbiological evidence of cryptococcal meningitis on cerebrospinal fluid if full cerebrospinal fluid results are not available at randomisation (e.g. cerebrospinal fluid CrAg test negative but culture on the same sample later returns positive for cryptococcal meningitis)

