### Criteria for discontinuing or modifying allocated interventions {11b}

Based on the following baseline laboratory abnormalities, participants may be withdrawn early (late exclusion) from the trial:DAIDS grade 4 neutropenia (absolute neutrophil count <0.4 × 10^9^/L)DAIDS grade 4 renal impairment (absolute creatinine level of ≥400 µmol/L)Microbiological evidence of cryptococcal meningitis, e.g. positive culture or microscopy, where participant was enrolled on a (presumed false) negative cerebrospinal fluid CrAg test

In the above scenarios, all study medication (regardless of treatment arm) is stopped, and the participant is referred to routine care for ongoing treatment.

If a participant is eligible and remains on the trial, study medication may be dose-adjusted or stopped under the following conditions:If a participant withdraws consent to continue study treatment, they are referred to routine care for ongoing treatment of their antigenaemia and HIV.If a participant experiences toxicity thought by the investigator to be related to study medication, the dose may be modified according to clearly defined guidelines in the study work practice documents. Fluconazole doses may be halved, and flucytosine doses may be halved (dosed twice daily) and then reduced further (daily dosing) if needed, with toxicity closely monitored and the dose adjusted up again as soon as possible. For cases in which intolerable toxicity persists despite dose reduction, study medication may be stopped. Alanine transaminase (ALT), renal function and a full blood count with differential are checked at baseline, and full blood count with differential is routinely repeated at day 15. Any abnormalities on day 1 guide additional ad hoc testing at the discretion of the clinician, guided by the work practice documents.As both drugs are renally excreted, baseline renal function guides dosing. If the eGFR (by Cockcroft Gault formula) is <50 ml/min, the fluconazole and flucytosine doses are halved. If the eGFR is <10 ml/min, the flucytosine dose is quartered.

At any time during the study, if a participant develops incident cryptococcal meningitis (not present at baseline), study medication is stopped and the participant is referred to routine care for treatment of their cryptococcal meningitis, though study follow-up continues per protocol.

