### Sample size {14}

Based on evidence from recent studies, we assume that the combined regimen of fluconazole plus flucytosine (intervention arm) could lead to a 40% relative reduction in mortality compared with fluconazole alone. From the ACTA trial [2, 31], the oral combination treatment had a mortality rate of 35% at 10 weeks, compared with 55%–70% mortality of fluconazole alone observed in clinical settings (i.e. a reduction of at least 36% mortality). We assume that 30% of blood CrAg-positive individuals identified during screening and treated with fluconazole alone die. This assumption is inferred from published data, including the REMSTART trial [15] in which 32% of blood CrAg-positive individuals treated with fluconazole (CD4 < 200 cells/µl) died over 6 months of follow-up. In South Africa, mortality was 25% in 2 cohort studies [16, 17].

Using a two-sided *α* = 0.05, a sample size of 540 (270 per arm) will provide 91% power to detect a 40% relative reduction in mortality with fluconazole alone versus flucytosine plus fluconazole (i.e. an observed mortality of 30% vs. 18%, respectively). The trial will also have 81% power to detect a 35% relative reduction if the effect size is smaller, and 83% power if mortality in the fluconazole arm is lower at 25%. Loss to follow-up was 2.5% in the REMSTART trial [15] over 12 months and <1% in the ACTA trial [2] over 10 weeks. A target of 600 participants will be enrolled, to conservatively account for up to 10% loss to follow-up in a pragmatic trial embedded in routine programmes.

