Analyses of survival data will be conducted using unadjusted and adjusted Cox regression analysis to calculate the hazard ratio (HR) and 95% CI between the treatment groups. Kaplan-Meier survival curves will also be plotted by treatment group, from which survival rates at 10 weeks and 6 months will be derived. A log-rank test will be performed to compare the survival curves between the treatment groups.

Primary analyses of efficacy outcomes will be based on the intention-to-treat population, and secondary analyses will be based on the per-protocol population. The safety analysis will be on the safety population. The frequency and proportions of participants developing clinical and laboratory-defined side effects (DAIDS grade 3 or 4 adverse events) will be summarised by treatment arm.

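### The set called intention-to-treat leaves out randomised participants who meet late-exclusion criteria, the criteria are stated inconsistently in an open-label trial, and the safety set inherits the omission

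*Protocol article*

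**What the plan says.** All places are in the protocol article.

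- **Analysis sets, {20c}.** The ITT definition begins inclusively: "All participants with valid informed consent will be included according to the treatment to which they are randomised", whatever the later protocol deviations. The next sentence takes some of them out: "Participants that meet late exclusion criteria will not be included in the intention-to-treat population". The safety set consists of ITT members who received at least one day of a study intervention.
- **Use of the set, {20a}.** "Primary analyses of efficacy outcomes will be based on the intention-to-treat population". The sensitivity analyses named there concern losses to follow-up and the per-protocol set.
- **Late exclusion criteria.** These cover "grade 4 abnormalities of platelets, neutrophil count, or creatinine level on baseline bloods", and also "Microbiological evidence of cryptococcal meningitis on cerebrospinal fluid if full cerebrospinal fluid results are not available at randomisation".
- **Discontinuation, {11b}.** For listed baseline abnormalities, "participants may be withdrawn early (late exclusion) from the trial". The list gives neutrophils, creatinine and microbiological evidence of meningitis, but not platelets. In those cases "all study medication (regardless of treatment arm) is stopped, and the participant is referred to routine care for ongoing treatment". A participant with incident meningitis also stops study drug but explicitly stays in follow-up.
- **Timing and blinding.** The schedule in {13} places blood count, creatinine, randomisation and first dose all on day 1. Section {16c} shows the arm on screen, and {17b} states that the trial is open-label.

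**The concern.** Late exclusions take effect after randomisation, often after the first dose, when site staff know the arm. The people concerned (very low neutrophils or platelets, severe renal impairment, or missed meningitis) can be expected to have high mortality, and mortality is the primary endpoint. Sections {12} and {17a} present all-cause mortality as the protection against open-label bias. That protection covers the counting of deaths. It does not cover the denominator if membership of the primary set can depend on a decision made with the arm known.

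Two further consequences follow from the text. Participants who received flucytosine or fluconazole and were then late-excluded disappear from the safety tables, although a grade 4 baseline abnormality makes their experience on drug relevant. And because {11b} withdraws them from the trial without saying that follow-up continues, their vital status may never be collected, in which case an all-randomised result could not be recovered later.

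**Working it through.** **1. Do the passages fix one rule?**

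| Item | Late exclusion criteria | {11b} | {20c} |
|---|---|---|---|
| Force | lists the criteria | permissive (may) | mandatory (will not) |
| Grade 4 platelets | listed | not listed | refers to the criteria without listing them |
| Cerebrospinal fluid | results incomplete at randomisation | enrolled on a presumed false-negative antigen test; no sample date | as above |

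A participant with grade 4 platelets leaves ITT under the first and third columns, but {11b} gives no ground for withdrawing that participant. On meningitis, the first column ties the criterion to a sample whose results were outstanding at randomisation. Section {11b} does not, and it separates these cases (withdrawn) from incident meningitis (followed up). Assigning a case to one or the other can need judgement after allocation is known.

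**2. Identical application.** Let *p* be mortality in participants who meet no criterion, equal in both arms under no effect. If everyone meeting a criterion is removed from both arms, both rates equal *p* and RR = *p*/*p* = 1.000. If everyone is kept in both arms, the rates are again equal. There is no bias in either case.

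**3. Uneven application, under assumptions.** The article gives neither the late-exclusion rate nor the mortality of those excluded. Assume *k* = 6 to 18 of 300 per arm (2% to 6%) meet a criterion, with mortality *m* = 50% to 70%. All are removed in the intervention arm and half in control.

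Control rate = [(300 − *k*)·*p* + (*k*/2)·*m*] / (300 − *k*/2); RR = *p* / control rate.

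With *p* = 30%, the control mortality in {14}:
- *k* = 6, *m* = 0.5: (88.2 + 1.5)/297 = 0.3020; RR = 0.993.
- *k* = 18, *m* = 0.7: (84.6 + 6.3)/291 = 0.3124; RR = 0.960.

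With *p* = 24%, the midpoint of the 30% and 18% in {14}:
- *k* = 6, *m* = 0.5: (70.56 + 1.5)/297 = 0.2426; RR = 0.989.
- *k* = 18, *m* = 0.7: (67.68 + 6.3)/291 = 0.2542; RR = 0.944.

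**4. A harsher split.** Remove all in the intervention arm and none in control, with *p* = 30%:
- 2% meeting a criterion, *m* = 0.5: control rate 0.98 × 0.30 + 0.02 × 0.5 = 0.304; RR = 0.987; two-sided error rate 5.1%.
- 5% meeting a criterion, *m* = 0.7: control rate 0.95 × 0.30 + 0.05 × 0.7 = 0.320; RR = 0.938; two-sided error rate 8.2%.

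For 2% to 5% meeting a criterion, the half-removal split gives error rates of 5.0% to 5.8%.

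**5. Direction.** The sign depends on which arm loses more. If control loses all and the intervention arm half (2% to 5% meeting a criterion), RR is 1.007 to 1.034.

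**The case against.** The strongest reply is that {20c} is mandatory and turns on meeting a criterion, not on a clinician's choice. The permissive wording in {11b} concerns withdrawal. Most criteria are numeric thresholds on day-1 bloods scheduled for every participant, and later deaths cannot alter them. Section {11b} stops medication in both arms alike, and {20c} requires set membership and reasons to be documented before database lock. This largely stands. It means a reader should not infer that the rule is discretionary throughout, or that the primary comparison has lost the protection of randomisation. Applied as {20c} reads, the laboratory criteria introduce no bias. Nor does the article support the idea that staff would act more readily on neutropenia in the flucytosine arm.

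A reader might also infer a power shortfall, since the inflation to 600 is made "to conservatively account for up to 10% loss to follow-up" only. That does not hold up. It needs an invented 5% late-exclusion rate on top of the full 10% loss, and even then power falls only from about 91% to 89%. With the 2.5% loss cited in {14} and the same 5%, 300 × 0.975 × 0.95 = 278 per arm remain, above the 270 required.

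Finally, the statistical analysis plan is not shown and may contain arm-blind flagging or further sensitivity sets. Their absence from an article is therefore not the point. What remains is what the article states: an ITT definition that removes randomised participants, criteria that disagree between sections, a cerebrospinal fluid criterion open to judgement, and a safety set restricted to ITT.

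**Conclusion.** The concern holds in a limited form. The set labelled ITT is a modified ITT set. It carries the primary analysis and narrows the safety analysis, and the passages defining who leaves it do not agree. Bias is a possibility, not a demonstrated fact: it requires uneven application between arms, most plausibly through the meningitis criterion. On assumed rates (2% to 6% meeting a criterion, 50% to 70% mortality among them, half of them kept in control and none in the intervention arm), the relative risk under no effect shifts by about 1% to 6%. That is small beside the 40% reduction the trial seeks, but it could matter for a borderline result. The omission of dosed participants from the safety set does not depend on any of these assumptions.

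**What to change.** 1. Define ITT as all randomised participants with valid consent, analysed as randomised, and report the present set as modified ITT. At minimum, rename the present set modified ITT and add an all-randomised sensitivity analysis.
2. Keep collecting 6-month vital status for late-excluded participants. First confirm that consent covers them: {18b} describes access to records for participants who cannot be reached, which may not extend to those withdrawn and referred to routine care.
3. Reconcile the Late exclusion criteria section, {11b} and {20c} on platelets, on permissive versus mandatory wording, and on the cerebrospinal fluid criterion. Which abnormalities lead to clinical withdrawal is for the trial team; the lists must agree.
4. For the modified ITT set, limit the criteria to specimens taken before the first dose, and flag members from those results without reference to arm.
5. Report late exclusions by arm and reason.
6. Define the safety set as all randomised participants who received study drug.

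The cost is a wording change in the protocol and analysis plan and a little tracing work. The downside is slight dilution of the estimated effect, because these participants stop study drug.

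### The safety population is nested in an ITT set that removes late exclusions, so participants who took study drug before late exclusion are left out of the by-arm adverse event summaries

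*Protocol article*

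**What the plan says.** Four parts of the protocol article combine here.

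- **Analysis sets, {20c}.** On the ITT population: "Participants that meet late exclusion criteria will not be included in the intention-to-treat population". The safety population is then "all study participants included in the ITT analysis who received at least one day of any of the study interventions".
- **Use of the set, {20a}.** "The safety analysis will be on the safety population". The endpoint concerned, in {12}, is the proportion of participants with DAIDS grade 3 or 4 adverse events, summarised by arm.
- **Late exclusion.** The Late exclusion criteria section names DAIDS grade 4 "abnormalities of platelets, neutrophil count, or creatinine level on baseline bloods", and also "Microbiological evidence of cryptococcal meningitis on cerebrospinal fluid if full cerebrospinal fluid results are not available at randomisation". Section {11b} says "Based on the following baseline laboratory abnormalities, participants may be withdrawn early (late exclusion) from the trial". It lists neutrophils, creatinine and microbiological evidence of meningitis, and adds that "all study medication (regardless of treatment arm) is stopped".
- **Timing, {13}.** Randomisation, the baseline full blood count and creatinine, and the first dose in both arms are all scheduled for day 1.

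Section {22} has grade 3 and 4 events and deaths entered in the electronic data capture system. All adverse events and deaths go to the Data Monitoring Committee, regulators and ethics committees.

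**The concern.** There can be a case for removing from an efficacy set people who prove ineligible on data fixed before treatment. That case does not carry over to safety, where what matters is having taken the drug. Because the safety set inherits the ITT removal, a person who took study drug and then met a late exclusion criterion is absent from both the numerator and the denominator of the safety tables.

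The people removed are not an arbitrary sample. They had poor marrow or renal values at baseline, or meningitis that was missed at entry. Section {11b} itself notes that both drugs are renally excreted and that baseline renal function guides dosing. The article presents the regimen as one that could be given safely to out-patients, so what happened to people who were dosed before their results came back is relevant to readers of the safety results.

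**Working it through.** **Step 1: set logic.** Let L be the participants who meet a late exclusion criterion, and T those with at least one day of any study intervention.

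- ITT = randomised with valid consent, minus L ({20c}).
- Safety = ITT and T ({20c}).
- Hence Safety contains no member of L, however much drug that member took. No other part of the article brings them back.

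**Step 2: can someone be in both L and T?** Yes. The qualifying bloods are drawn on the day dosing starts ({13}). The cerebrospinal fluid criterion covers results that arrive after randomisation. Section {11b} speaks of stopping medication, which presupposes that it may have begun.

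**Step 3: do the definitions of L agree?** Not fully.

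- The Late exclusion criteria section includes grade 4 platelets; the list in {11b} does not.
- Section {11b} says such participants may be withdrawn, whereas {20c} removes anyone who meets the criteria. A participant kept on drug could therefore still be missing from the safety set.

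**Step 4: size.** The plan gives no number of late exclusions and no expected event rate, so there is no stated figure to reproduce. All inputs below are assumptions except the target of 600 ({14}). Let f be the fraction dosed and late-excluded, p_all the event rate in all treated, p_kept the reported rate, and p_drop the rate in those removed:

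p_all = (1 − f) × p_kept + f × p_drop, so p_kept = (p_all − f × p_drop) / (1 − f).

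Example with f = 3%, p_drop = 40%, p_all = 15%:

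- p_kept = (0.15 − 0.03 × 0.40) / 0.97 = 0.138 / 0.97 = 14.2%, a shift of 0.8 percentage points.
- In counts: 600 × 0.03 = 18 people and 18 × 0.40 = 7.2 expected events removed; (90 − 7.2) / (600 − 18) = 82.8 / 582 = 14.2%.

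Range with the reported rate held at 20%:

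| Dosed and late-excluded | People of 600 | All-treated rate if p_drop = 50% | All-treated rate if p_drop = 80% |
|---|---|---|---|
| 1% | 6 | 0.198 + 0.005 = 20.3% | 0.198 + 0.008 = 20.6% |
| 3% | 18 | 0.194 + 0.015 = 20.9% | 0.194 + 0.024 = 21.8% |
| 5% | 30 | 0.190 + 0.025 = 21.5% | 0.190 + 0.040 = 23.0% |

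**Step 5: direction.** Rearranging, p_all − p_kept = f × (p_drop − p_kept). The reported rate is too low only if those removed have more events than those kept. If the two rates are equal, nothing changes.

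**The case against.** The strongest reply is that the defect is narrow and that several larger claims a reader might draw from it fail.

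- **That the events disappear.** They do not. Section {22} keeps them in the database and before the Data Monitoring Committee, regulators and ethics committees. Section {20c} also requires reasons for exclusion from each set to be documented before database lock. The loss is confined to the by-arm analysis tables. This limits the point but does not answer it, since those tables are the planned safety analysis.
- **That the bias falls mostly on the flucytosine arm.** The documents do not show this. The laboratory criteria are baseline values and the meningitis criterion concerns samples pending at randomisation, so removal is balanced between arms in expectation, and medication is stopped in both. A difference between arms would need extra flucytosine toxicity during the exposure before stopping, and no figure is given for that.
- **That the qualifying abnormality is itself a lost adverse event.** It is not. Section {22} counts only worsening from baseline or new abnormalities. What is lost is later toxicity in these people.
- **That the one-day threshold loses further exposed participants.** This is nearly empty. Both arms take fluconazole once daily and a day of any study intervention qualifies, so one fluconazole dose is enough.
- **That restoring these participants gives complete data.** It may not. They are withdrawn and referred to routine care, and event follow-up ends at withdrawal ({22}). Their short observation would itself lower the observed proportion. This stands, and it is why a separate listing is needed as well.

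Safety is also a secondary endpoint. The nesting of the safety set does not touch the primary mortality comparison or its power.

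**Conclusion.** The point holds in its narrow form. By the article's own definitions, no late-excluded participant can enter the safety analysis, although the protocol foresees that some will have taken study drug. This follows from the text and needs no outside figure.

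Reported grade 3 or 4 rates would be understated if those removed have more events than those kept. That is plausible given their baseline state, but it is not documented. In the illustrations the shift runs from 0.3 points (1% removed, 50% against 20%) to 3.0 points (5% removed, 80% against 20%), with 0.8 points in the 15% example. All of these rest on assumed late-exclusion fractions and event rates. Neither the true size nor any difference between arms can be derived from the documents. The definition should be corrected because it gives the wrong set for safety and is cheap to change.

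**What to change.** - Define the safety population without reference to ITT: all randomised participants who took at least one dose of any study drug, analysed by treatment received, including those who later meet late exclusion criteria.
- List late exclusions separately by arm, with the criterion met, the exposure, and events up to withdrawal. State that their follow-up may be truncated, and show the grade 3 or 4 proportions with and without them.
- Reconcile the Late exclusion criteria section with {11b} on platelets, and {11b} with {20c} on whether meeting a criterion or being withdrawn decides membership. Which clinical list governs is for the investigators.

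Section {20c} fixes set membership before database lock, so the change belongs before then. It costs a sentence in the definition and one listing, with no change to sample size or trial procedures, and the events concerned are already recorded. The downside is possibly slightly less favourable safety rates and some participants with short observation in the denominator.
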